### Measures

Data will be collected via an online structured questionnaire developed specifically for this study. The questionnaire has two main sections. The first includes nine closed-ended items (multiple-choice questions) assessing participants’ general background and experience working with bereaved patients. The second presents seven brief, hypothetical clinical vignettes created for this study to measure knowledge and application of PGD diagnostic criteria. For each case vignette, participants will be asked a closed-ended question, indicating whether they believe the case is likely to meet the diagnostic criteria for PGD or not (Study Protocol Appendices).

*Intervention:* After completing the initial questionnaire, half of the participants (experimental group) will view a 3-minute informational video providing concise evidence-based material on PGD, including core diagnostic criteria and clinical applications. The other half (control group) will view a 3-minute video presenting general information on the importance of promoting research, diagnosis, and tailored care for older adults experiencing bereavement, without reference to PGD. Videos are structurally matched in terms of graphics, duration, and word count to control for potential confounding variables. The rationale for presenting the explanatory material through a video rather than written text is grounded in empirical findings indicating that video-based instruction enhances learning effectiveness, particularly in the acquisition of clinical skills among healthcare professionals [e.g (25, 26) This advantage is attributed, among other factors, to the increased engagement, concentration, and interest elicited by video presentations compared to traditional text-based materials.

### Procedure

Ethical approval for the study was obtained from the Ruppin Academic Center Institutional Ethics Committee and the Helsinki Committee of Clalit Health Services. Participants will receive online invitations, including an explanation of the study purpose, participation procedure, and assurance of full anonymity. It will also be emphasized to participants that the questionnaire contains hypothetical scenarios intended solely to assess professional responses and does not include personal questions or require emotional disclosure. However, it will be clarified that the content may evoke uncomfortable feelings, and that participation can be discontinued at any point without any consequences. Participation will be voluntary and contingent upon providing informed consent.

In the first stage, participants will complete the online questionnaire, including background items and seven vignettes, estimated to take six minutes. The case vignettes will be presented in a randomized order for each participant to control potential order effects. Upon completing the questionnaire up to this point, participants will be asked to click the ‘Submit’ button, after which they will be prompted to indicate whether they wish to continue to the next phase of the study. This procedure is intended to ensure that the data of participants who choose not to continue are preserved and not lost. Participant responses across study stages will be linked using an identifier code, allowing for repeated-measures analyses while maintaining participant anonymity. In the second stage, participants will be individually randomized (1:1) via a computer-generated sequence in a partially participant-blinded, assessor-blinded controlled trial to either the experimental group (PGD video) or the control group (general bereavement video). In the third stage, all participants will re-answer the seven vignettes to assess the intervention’s effect on knowledge and application, taking approximately four minutes. Following completion of this stage, all participants will be asked whether they are willing to participate in a follow-up assessment. Those who consent will, at one month, receive an automated link to complete the clinical vignettes again to assess retention of the intervention effects (fourth stage). An overview of the study design is shown in **Figure 1**.

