**Figure 1 f1:**
[figure not shown]
Study design.

Upon completion of their participation, participants in the control group will be provided access to the PGD video to ensure equitable access to professional information; this will occur immediately after the third stage for those who do not consent to follow-up, and after completion of the one-month follow-up assessment for those who do. All collected data will be stored anonymously and encrypted, with access limited to authorized researchers for study purposes only. Participants will remain anonymous throughout, and results will be reported only in aggregate form.

*Data Analysis:* To test the study hypotheses, data analysis will include descriptive and inferential statistics, including simple linear regression, one-way analysis of covariance (ANCOVA) controlling for relevant background variables (e.g., levels of professional training), and mixed-design repeated measures ANCOVA.

*Feasibility assessment:* A preliminary feasibility assessment (N = 20 physicians, of whom 16 were senior physicians) was conducted to evaluate the study procedures and materials. Baseline performance on the clinical vignettes yielded a mean correct response rate of 61.4%, broadly consistent with prior reports in the literature (e.g (27). Overall, 12 participants completed both pre- and post-intervention assessments. Preliminary patterns suggested a potential intervention effect: in the control group, correct responses increased from 59.1% pre-intervention to 65.7% post-intervention, whereas in the experimental group, correct responses increased from 63.3% to 83.7%. These observations should be interpreted with caution given the small sample size and exploratory nature of this feasibility assessment and are presented solely to support the practicality and potential utility of the study design.

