To address these challenges, several strategies have been incorporated into the study design. To enhance recruitment feasibility, formal collaboration agreements were established with key professional leaders in the relevant medical fields (including the Chair of the Israeli Geriatrics Association, the Chief Geriatrician of the largest health maintenance organization in Israel, and others), supporting coordinated dissemination of the study invitation and increasing the likelihood of broad participation. To mitigate potential selection bias, the study will aim to ensure balanced representation across medical specialties and levels of professional training. In order to reduce limitations associated with the online format and potential lapses in attention, the intervention will be delivered through a concise animated video, an evidence-based educational modality shown to improve engagement and cognitive processing, as previously described in the Methods section. The questionnaire was intentionally kept brief to minimize participant effort, and after completing the initial knowledge-mapping stage, participants will have the option to discontinue or proceed with the intervention, with responses from the first stage retained for all participants. Follow-up analyses will examine potential differences between those who continue and those who discontinue, allowing identification of any systematic attrition patterns. Finally, to reduce self-report bias, the study is conducted anonymously, which is expected to limit socially desirable responding. In addition, the use of clinical vignettes provides a performance-based assessment of diagnostic application, thereby reducing reliance on self-reported knowledge and strengthening the validity of the evaluation.

Ultimately, this study seeks to reduce suffering and enhance both quality of life and psychological resilience among older adults. At a time when scientific focus is often on advanced technologies and cutting-edge research, the value of this work lies in its simplicity and practical orientation. Its strength stems from translating current scientific knowledge into clear, actionable tools that can meaningfully improve clinical practice and the quality of care delivered to older patients.

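### Agreement to the one-month follow-up is sought after randomisation, video and post-test, so the retention comparison is made in groups selected after exposure, and the described attrition check is tied to the pre-randomisation exit

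*Protocol article*

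**What the plan says.** The Procedure section of the protocol article fixes the order of events. Participants answer the background items and the seven vignettes, submit, and say whether they wish to go on. Next, "participants will be individually randomized (1:1) via a computer-generated sequence" to one of two videos, in a "partially participant-blinded, assessor-blinded controlled trial". Then comes the post-test: "In the third stage, all participants will re-answer the seven vignettes to assess the intervention’s effect on knowledge and application". Only after that does the follow-up question appear: "Following completion of this stage, all participants will be asked whether they are willing to participate in a follow-up assessment". The fourth stage is limited to those who say yes: "Those who consent will, at one month, receive an automated link to complete the clinical vignettes again".

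The paragraph after Figure 1 ties control-group access to the PGD video to that answer. For controls who decline, "this will occur immediately after the third stage for those who do not consent to follow-up"; controls who agree get it after completing the one-month assessment.

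Expected results places persistence at one month under the primary outcomes, and Aims includes long-term impact. Practical and operational considerations describes one attrition analysis: "Follow-up analyses will examine potential differences between those who continue and those who discontinue, allowing identification of any systematic attrition patterns". The sentence just before it concerns the option to stop after the initial knowledge-mapping stage.

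**The concern.** Membership of the one-month comparison is decided after exposure. By then the arms have watched different material under partial blinding and have taken a post-test on which the protocol expects them to differ. In the feasibility work the post-test means were 83.7% and 65.7%. Willingness to return may therefore depend on arm, on performance, or on both together. If it does, the one-month groups are no longer comparable by randomisation, and a difference between them mixes retention with selection.

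The attrition check as worded looks mainly at another exit. Stopping after stage 1 happens before allocation. It limits who the results apply to, but it cannot unbalance the arms. Loss at stages 3 and 4 can, and no comparison by arm is described for those stages.

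At stake is the persistence part of the second primary outcome.

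**Working it through.** **1. The plan's own figures.** For a two-group, two-measurement interaction, λ = f²·N·m/(1-ρ), with f² = η²/(1-η²), m = 2, and df 1 and N-2. The correlation ρ = 0.5 is an assumption; the article gives none.
- η² = 0.06: f² = 0.0638, N = 34, λ = 0.0638 × 34 × 2/0.5 = 8.68, power 81.5%.
- η² = 0.01: f² = 0.0101, N = 198, λ = 0.0101 × 198 × 2/0.5 = 8.0, power 80.4%.

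Both stated sample sizes reproduce. The small effect corresponds to a difference in change of 4f = 4 × 0.1005 = 0.40 SD. That is a difference in *change*, which matters in step 4.

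**2. Selection model (all inputs assumed).** The article gives no one-month agreement rate and no relation between score and willingness. Suppose there is no true effect at one month, all scores have SD 1, and logit(agree) = 0.4 + b·post. Two scenarios: b = 0.5 in one arm and 0 in the other; or 0.5 in one and -0.5 in the other. With 2,000,000 draws per arm, agreement is 59 to 60% in both arms in both scenarios, so comparing rates alone would not show the problem. Selection creates an arm difference D in mean post-test score among those who agree: D ≈ 0.192 SD in the first scenario and 0.385 SD in the second.

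**3. What D does to each possible retention contrast.** Selection acts only through the post score, so each other score shifts by its correlation with post times D. Take the pre-post and post-month correlations as 0.6.

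| Contrast | Formula | b = (0.5, 0) | b = (0.5, -0.5) |
|---|---|---|---|
| Raw one-month score | 0.6·D | 0.115 | 0.231 |
| One-month score adjusted for baseline, pre-month correlation 0.6 | ≈ 0.6·D × (1-0.6) | 0.046 | 0.092 |
| The same, pre-month correlation 0.36 | ≈ 0.6·D × (1-0.36) | 0.074 | 0.148 |
| Post-to-month change | (0.6-1)·D | -0.077 | -0.154 |
| Pre-to-month change | (0.6-0.6)·D | 0 | 0 |

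Direct simulation agrees: 0.048 and 0.093, then 0.075 and 0.151, for the baseline-adjusted rows; zero to within 0.002 for pre-to-month change; and zero to within 0.001 after adjusting for both baseline and post score.

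**4. How far this carries.** The zero for pre-to-month change needs equal pre-post and post-month correlations. If they were 0.5 and 0.7, the second scenario would give (0.7-0.5) × 0.385 = 0.08 SD; reversed, -0.08 SD. Setting the raw 0.115 and 0.231 SD against 0.40 SD is not a valid comparison, because one is a difference in scores and the other a difference in change.

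**5. If willingness depends on something unrecorded.** Let willingness correlate 0.2 to 0.5 with the part of the one-month score that baseline does not explain, in the same direction in both arms, with assumed agreement of 70/50, 80/50 or 70/30% (experimental/control). The spurious difference is then 0.06 to 0.33 residual SD, against the arm with the higher agreement. With equal rates and the same selection in both arms it is zero.

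**The case against.** The strongest reply concerns size. Data Analysis names a mixed-design repeated-measures ANCOVA and the hypothesis is about improvement, so a raw one-month difference is not the planned contrast. Under the model above the bias in pre-to-month change can cancel, and selection on an observed post score can be handled in the analysis by a method the full plan may specify. This stands. A reader might infer that selection could produce over half of the effect N = 198 is sized for; the documents do not support that, for the reason in step 4.

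A second inference to resist is that controls will decline in order to see the PGD video sooner. The article does not say that participants know the timing when they answer, and holding the video back from those who agree keeps them unexposed until the assessment. The incentive is only a possibility, and the point does not need it.

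Third, the promise to identify any systematic attrition patterns could be read to cover the fourth stage. Its wording does not exclude that, but its placement points to the stage-1 exit and no arm is mentioned.

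Finally, asking earlier does not stop people who agreed from failing to respond, and it may deter some from going on, when only 12 of 20 completed both pre and post in the feasibility work. Both are fair and shape the remedy. None of this changes the order of events, which the article fixes.

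**Conclusion.** The point holds as a risk of bias in the retention comparison, not as a demonstrated bias. The one-month groups are selected after exposure, and the described check is worded around an exit that cannot unbalance the arms. Size and direction are unknown. Under the assumed selection on the post score, the figures are about 0.05 to 0.15 SD for the baseline-adjusted one-month score, -0.08 to -0.15 SD for post-to-month change, and near zero for pre-to-month change when the two correlations match. They rest on assumed correlations, about 60% agreement, and selection that differs by arm, for which the article gives no evidence either way. They are not an upper limit if willingness depends on something unrecorded.

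A reader might extend the point to the whole trial. The documents do not support that: the immediate pre-post comparison is complete before the follow-up question is asked. The change is worth making because it is cheap and the weakness lies in the design, where analysis can only partly repair it.

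**What to change.** - Ask for one-month agreement at the existing prompt at the end of stage 1, before randomisation. Make it optional and not a condition of continuing.
- Send the one-month link to everyone who agreed, and make the retention comparison in that set. Agreement is then fixed before allocation, so the arms within the set are randomised.
- Report non-completion at stages 3 and 4 by arm, with baseline scores and, for stage 4, post-test scores. Rates alone are not enough (step 2).
- Include the baseline and post-test scores of non-completers in the retention analysis. This deals with non-response that depends on those scores, not with non-response that depends on unrecorded interest.
- Controls who declined before randomisation can still receive the PGD video after stage 3, since they are outside the one-month set. Controls who agreed receive it at the one-month assessment or when its window closes. That covers those who agree but never complete, for whom the present text states no access.

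Cost: moving one online question and a small ethics amendment. A few people may stop at the earlier prompt. Earlier agreement does not prevent later non-response, which is why the by-arm report is still needed.

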**Figure 1 f1:**
[figure not shown]
Study design.

Upon completion of their participation, participants in the control group will be provided access to the PGD video to ensure equitable access to professional information; this will occur immediately after the third stage for those who do not consent to follow-up, and after completion of the one-month follow-up assessment for those who do. All collected data will be stored anonymously and encrypted, with access limited to authorized researchers for study purposes only. Participants will remain anonymous throughout, and results will be reported only in aggregate form.

*Data Analysis:* To test the study hypotheses, data analysis will include descriptive and inferential statistics, including simple linear regression, one-way analysis of covariance (ANCOVA) controlling for relevant background variables (e.g., levels of professional training), and mixed-design repeated measures ANCOVA.

*Feasibility assessment:* A preliminary feasibility assessment (N = 20 physicians, of whom 16 were senior physicians) was conducted to evaluate the study procedures and materials. Baseline performance on the clinical vignettes yielded a mean correct response rate of 61.4%, broadly consistent with prior reports in the literature (e.g (27). Overall, 12 participants completed both pre- and post-intervention assessments. Preliminary patterns suggested a potential intervention effect: in the control group, correct responses increased from 59.1% pre-intervention to 65.7% post-intervention, whereas in the experimental group, correct responses increased from 63.3% to 83.7%. These observations should be interpreted with caution given the small sample size and exploratory nature of this feasibility assessment and are presented solely to support the practicality and potential utility of the study design.

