### Expected results

The *primary outcomes* of the study are twofold. First, participants are expected to report significant knowledge gaps regarding PGD diagnostic criteria, reflecting difficulty or uncertainty in applying these criteria with older bereaved patients. Second, exposure to concise PGD-related information via a video-based intervention (with a control group viewing an equivalent video; see Methods) is expected to improve knowledge and application of diagnostic criteria. Specifically, correct responses on the clinical vignettes are expected to increase in both groups following the intervention, with a greater improvement in the experimental group compared to the control group. These improvements are expected to persist at one-month follow-up, particularly in the experimental group.

The *secondary outcome* concerns differences between medical specialties. Psychiatrists are expected to demonstrate higher baseline knowledge and application of PGD criteria compared to other participants, achieving a significantly higher proportion of correct responses on the clinical vignettes.

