## Methods and analysis

### Participants

The study will employ a mixed experimental design. The target population includes senior physicians and residents in geriatrics, psychiatry, and family medicine working in diverse settings, including hospitals, clinics, geriatric centers, and private practices, who have frequent contact with older adults. Participation will be anonymous, voluntary, and based on informed consent. The sample will be recruited via convenience sampling through professional channels (e.g., mailing lists of relevant medical associations, professional social networks, and distribution via department and center administrators), aiming to ensure balanced representation across medical specialties and levels of professional training.

*Sample size:* Power analysis using G*Power (version 3.1) indicated that to detect a medium effect size (partial η² = 0.06) with 80% power and α = 0.05 in a mixed repeated-measures design with two independent variables, a minimum sample of 34 participants is required. To detect a small effect size (partial η² = 0.01) under the same conditions, 198 participants are needed. Accordingly, the study aims to recruit a sample size within this range.

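### No baseline-score adjustment is named for the intervention test; the group-by-time test the article points to is valid but less precise than ANCOVA on the baseline vignette score

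*Protocol article*

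**What the plan says.** The Data Analysis paragraph of the protocol article (at the end of Procedure) gives an open list of methods: descriptive statistics, simple linear regression, "one-way analysis of covariance (ANCOVA) controlling for relevant background variables (e.g., levels of professional training), and mixed-design repeated measures ANCOVA". No model is matched to a hypothesis. The background covariates are attached to the one-way ANCOVA; none is named for the repeated-measures model.

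Expected results predicts that correct vignette responses will rise in both arms, "with a greater improvement in the experimental group compared to the control group", and that the gain will persist at one month.

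The sample-size paragraph under Participants is set "to detect a medium effect size (partial η² = 0.06) with 80% power and α = 0.05" and continues "in a mixed repeated-measures design with two independent variables, a minimum sample of 34 participants is required". For the smaller effect it says: "To detect a small effect size (partial η² = 0.01) under the same conditions, 198 participants are needed".

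Under Procedure, all seven vignettes are answered before the video, then "participants will be individually randomized (1:1) via a computer-generated sequence". The vignettes are answered again afterwards and, for those who agree, at one month. An identifier code links the stages, so each randomised participant's baseline score is available to the analysis.

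**The concern.** The baseline score is measured before randomisation, on the same seven vignettes as the outcome, and is likely to be its best single predictor. In a group-by-time analysis it is used only as one of the repeated outcomes. The test then subtracts it in full, as if the post-video score tracked baseline one for one, when the regression slope is usually below one. The cost is precision, plus a conditional error whenever the arms happen to differ at baseline.

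This matters more here than in a large trial. The target is only a range from 34 to 198, the sample is a convenience sample of busy physicians, and 12 of the 20 feasibility participants completed both the pre- and post-video assessments. Precision available at no cost is worth taking.

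**Working it through.** **Inputs.** From Participants: partial η² of 0.06 and 0.01, power 80%, α 0.05, a mixed repeated-measures design. From Procedure: two arms, 1:1. From the Feasibility assessment: 59.1% to 65.7% (control) and 63.3% to 83.7% (experimental). The pre-post correlation ρ is not stated. It is an assumption here, shown at 0.3, 0.5 and 0.7. The formulas take equal variance σ² before and after the video.

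**Step 1: reproduce the stated sample sizes.** Interaction test in a mixed design with k groups and m waves: f² = η²/(1−η²), λ = f²·N·m/(1−ρ), with (k−1)(m−1) and (N−k)(m−1) degrees of freedom. Put k = 2, m = 2, ρ = 0.5:

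- η² = 0.06: f² = 0.0638; N = 34 gives λ = 0.0638 × 34 × 2/0.5 = 8.68; power 0.815.
- η² = 0.01: f² = 0.0101; N = 198 gives λ = 0.0101 × 198 × 2/0.5 = 8.00; power 0.804.

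Both figures match. The within-subject time test gives the same numbers when k = m = 2. Three waves at ρ = 0.5 give 28 and 162; two waves give 46 and 274 at ρ = 0.3, and 22 and 120 at ρ = 0.7. A between-groups test (two waves, ρ = 0.5) gives 96 and 586. So the plan's numbers fit a two-wave repeated-measures test with ρ = 0.5.

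**Step 2: compare the variances.** With two waves the interaction test is a two-sample test on change scores.

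- Change score: variance proportional to 2(1−ρ)σ².
- Post score adjusted for baseline: (1−ρ²)σ².
- Ratio, adjusted to change: (1−ρ²)/[2(1−ρ)] = (1+ρ)/2, below 1 for every ρ below 1.

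| ρ | Ratio | Variance reduction | SE reduction |
|---|---|---|---|
| 0.3 | 0.65 | 35% | 19% |
| 0.5 | 0.75 | 25% | 13% |
| 0.7 | 0.85 | 15% | 8% |

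At ρ = 0.9 the variance reduction is 5%. Simulation at ρ = 0.5, with the slope estimated from the data, gave ratios of 0.79 at N = 34 and 0.76 at N = 198, so little is lost to estimating it.

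**Step 3: translate into N and power.** The plan's effects correspond to a difference in change of 4f: 1.01σ and 0.40σ. Same raw effect, 80% power:

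| ρ | Medium effect: N, change / adjusted | Small effect: N, change / adjusted |
|---|---|---|
| 0.3 | 46 / 32 | 274 / 180 |
| 0.5 | 34 / 26 | 198 / 148 |
| 0.7 | 22 / 18 | 120 / 102 |

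At ρ = 0.5 with N unchanged, power rises from 0.815 to 0.909 (N = 34) and from 0.804 to 0.901 (N = 198).

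**Step 4: chance imbalance.** Given a baseline gap Δ between arms, the change-score estimate is displaced by about −(1−ρ)Δ. In simulation at ρ = 0.5 the slope on Δ was −0.48 (N = 34) and −0.49 (N = 198), against about 0 for the adjusted estimate.

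The feasibility figures illustrate the arithmetic only. "in the control group, correct responses increased from 59.1% pre-intervention to 65.7% post-intervention" is a rise of 6.6 points; the experimental arm rose 83.7 − 63.3 = 20.4. The difference in change is 13.8, the post-video difference is 83.7 − 65.7 = 18.0, and the baseline gap is 63.3 − 59.1 = 4.2. With slope b the adjusted estimate is 18.0 − 4.2b: 16.7, 15.9 and 15.1 for b = 0.3, 0.5 and 0.7. At 0.5 it lies 2.1 points above the change-score figure, which is (1−0.5) × 4.2.

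**The case against.** The strongest reply is that this is a condensed article. Its covariate list is open and gives training level only as an example. It assigns no model to the intervention test. A repeated-measures ANCOVA of the two post-video waves with baseline as covariate is not excluded, and a full protocol or SAP may name it. Group by time also answers the stated hypothesis directly, and choosing a valid but less efficient test is not an error.

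Much of this stands, and it rules out several stronger readings that a reader might infer:

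- That the plan never adjusts for baseline. The article supports only that no such adjustment is named. Hypothesis, power calculation and model make group by time the natural reading, not a certain one.
- That a quarter of the precision is lost outright. That figure needs ρ = 0.5. The sample sizes reveal the value that went into the power calculation, not the correlation a seven-item score will show.
- That baseline imbalance biases the result. The change score already subtracts baseline and is unbiased over randomisation. What remains is a conditional over-correction of opposite sign. The 4.2-point feasibility gap comes from a very small sample that the article itself says to read with caution.
- That an unadjusted post-video comparison is planned. Nothing says so; the one-way ANCOVA fits the specialty comparison at baseline, where the baseline score is the outcome.

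How the one-month contrast is isolated within a three-wave model, and how the two time points are ordered for testing, are details usually left to an SAP and are not part of this point.

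What the reply does not remove is that the article's own hypothesis, model and power paragraph all point to the less precise of two valid analyses, although the data for the better one are already collected and linked.

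**Conclusion.** The point holds as a free improvement, not as an error of validity. On the natural reading the intervention effect is tested by group by time. With two waves this has a larger variance than ANCOVA on the baseline score: adjustment would remove 25% of the variance if ρ is 0.5, and between 35% and 15% for ρ from 0.3 to 0.7. At the plan's own inputs that is the difference between about 80% and about 90% power at the same N. The direction does not depend on ρ; the size does, and it shrinks as ρ approaches 1. The figures assume equal pre and post variance and a linear relation between the two scores. The conclusion is conditional on no unseen document already naming the adjustment.

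**What to change.** State in the Data Analysis paragraph that the primary intervention analysis is an ANCOVA of the post-video vignette score on arm, with baseline vignette score, specialty and training level as covariates, and report the adjusted arm difference with its 95% confidence interval. Use the same model for the one-month score. Keep the mixed-design repeated-measures model as supportive. If a full protocol or SAP already specifies baseline adjustment, say so in the article.

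The cost is a few sentences. The baseline score and background items are already collected and linked, and neither the procedure nor the recruitment range has to change. The extra precision is best kept as a margin against attrition rather than used to lower the target, because ρ is unknown.
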